While there is some evidence of well-being and mental health benefits from spiritual meditation practices [30], to our knowledge there is no longitudinal empirical evidence on the long-term effects of prolonged spiritual meditation practice. A cross-sectional survey by our team including both secular and spiritual meditation practitioners with varying lifetime practice history found a dose-response plateau between historical practice hours and psychological well-being outcomes after 500 hours of practice [31]. This survey also found that meditating at a regular time each day was associated with positive outcomes, supporting the hypothesis that regularity of practice may be more impactful than intense but irregular sets. Follow-up surveys at 2 months and 2-4 years with this same sample found both practice dose, that is, hours per month, and practice frequency significantly predicted improvements in life satisfaction, affect, and psychological distress [32]. However, these participants’ varying lifetime practice history introduces possible survivor bias effects (ie, only those who had already been benefiting from regular practice over the years signed up to complete these surveys) and obscures the effects of initiating a regular practice. Moreover, this study was not preregistered, included very heterogeneous types of meditation practice, and used a rough estimate of practice during the 2-4 year follow-up. To address these gaps, a preregistered longitudinal study focused on those initiating a regular practice is required.

To our knowledge, there is only one study that compares the outcomes of an explicitly spiritual meditation practice to a control group that includes secular meditation practices [33]. In this study of 31 participants, a program (Dharma in Daily Life) that emphasized both regular meditation and integration of Buddhist teachings showed greater improvement in subjective well-being (but not quality of life) than continued meditation practice as usual over a 2-year intervention period. However, while the meditation as usual group included secular practices, it also contained participants who engaged in some other spiritual meditation practices (eg, Vipassana and Zen), and all participants in both groups had some familiarity with Buddhism. A further study is necessary to disentangle the potential moderating effects of spiritual and secular meditation contexts on quality of life and mental well-being.

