Finally, the study aims to document the incidence and impact on daily function of any challenging, difficult, or distressing meditation-related experiences (Aim 6). Meditation-related adverse effects (MRAEs) will be defined as any challenging, difficult, or distressing meditation-related experiences that impact everyday functioning. Our aims, hypotheses, and possible interpretations are summarized in Table 1 below.

**Table 1. T1:** Protocol Design table.

Question	Hypothesis	Sampling plan (eg, power analysis)	Analysis plan	Interpretation given to different outcomes
Does regular meditation practice after initial instruction increase quality of life?	The amount of meditation practice during approximately the first year predicts practitioners’ quality of life, such that a greater amount leads to greater quality of life.	A total number of 522 gives 95% power to detect the variance in quality of life (EQ-HWB-9^a^) explained by monthly meditation practice observed in linear mixed model analysis, at a 2-tailed significance level of 0.05, accounting for an estimated 20% loss to follow-up.	Linear mixed model of the fixed effect of the amount of meditation in the past month on quality of life in the past week (EQ-HWB-9), controlling for the confounding factors of age, caring status, education, mental health diagnosis, commitment to meditation, and membership of a practice support community at baseline.	A positive/negative and statistically significant association between the amount of meditation in the past month on quality of life and in the past week will suggest that regular meditation practice after initial instruction increases/decreases quality of life in a linear fashion. A nonsignificant association will suggest an absence of evidence for either of these effects.

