Does regular meditation practice after initial instruction increase mental well-being?	The amount of meditation practice during approximately the first year predicts practitioners’ mental well-being, such that a greater amount leads to greater mental well-being.	A number of 242 gives 95% power to detect the variance in mental well-being (SWEMWBS^b^) explained by monthly meditation practice observed in linear mixed model analysis, at a 2-tailed significance level of 0.05, accounting for an estimated 20% loss to follow-up.	Linear mixed model of the fixed effect of the amount of meditation in the past month on mental well-being in the past 2 weeks (SWEMWBS), controlling for the confounding factors of age, caring status, education, mental health diagnosis, commitment to meditation, and membership of a practice support community at baseline.	A positive/negative and statistically significant association between the amount of meditation in the past month on mental well-being in the past 2 weeks will suggest that regular meditation practice after initial instruction increases/decreases mental well-being in a linear fashion. A nonsignificant association will suggest an absence of evidence for this.
Is the effect of continued meditation practice after initial instruction on quality of life moderated by whether a practitioner’s meditation tradition is spiritual or secular?	Whether the meditation tradition is secular or spiritual will moderate any effects on quality of life (nondirectional)	Sampling plan follows hypothesis 1, with an additional 20%, n=627, powered to detect effect of f^2^=0.0318	Linear mixed model of the fixed effect of the amount of meditation in the past month and the interaction effect of tradition spirituality on quality of life in the past week (EQ-HWB-9), controlling for the confounding factors of age, caring status, education, mental health diagnosis, commitment to meditation, and membership of a practice support community at baseline.	A positive/negative statistically significant beta coefficient for this interaction will indicate that regular meditation practice within a spiritual tradition will have a larger/smaller effect on quality of life than practicing within a secular tradition. A nonsignificant association will suggest absence of evidence for this.

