### Measures

A schedule of measures is shown in Table 3 and described in detail below.

Meditation practice frequency and duration will be assessed weekly. Participants will be asked how many days they practiced in the past week, the average number of sessions per day, and the average minutes per session. This is a weekly modification of the timeline followback method, which is the gold standard for reporting in substance use literature, and has been validated for exercise reporting [32] and online administration [56]. We have also validated this question format against a log of meditation timer practice data [32]. Weekly measurement supports accurate reporting in similar methods [57], while allowing us to calculate the amount of meditation each month. This will be our independent variable.

Meditation practice characteristics, including type (eg, meditation with movement such as walking meditation or mindful observation such as observing thoughts or emotions), guided versus unguided sessions (eg, “I work with a teacher or instructor” or “My practice is self-guided”), and social context of their practice (eg, “I practice in a group” or “I practice alone”), will be recorded monthly. These measures will be used to describe the sample by reporting the frequency of each practice type and context reported by participants over one year.

Secular or spiritual meditation practice will be assessed at baseline and monthly by a single item (“In the past month, what meditation traditions have you practiced in?”). Participants will be divided into 2 groups at follow-up; those who both nominated secular meditation as their tradition at baseline and reported a maximum of one month of practice in any spiritual tradition over the follow-up period, versus all participants who practiced in spiritual traditions for 2 months or more during the year. This division will facilitate investigating if those meditation practitioners who practice in spiritual traditions experience the same effects as secular practitioners, while allowing for some dabbling in different traditions by participants. This will be a covariate.

Commitment to meditation practice will be assessed at baseline with a single item (“How committed are you to practicing meditation?” Rate 1‐10). This will be a covariate.

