Community of practice membership will be assessed by a single item and recorded at baseline and one year (“Are you an active member of a community of practice [eg, sangha, meditation group, or online communities]? Yes/No”). This will be a covariate.

Age in years will be recorded at baseline. This will be a covariate.

Caring status, including type of caring relationship, will be assessed at baseline. This will be a covariate.

Education will be assessed by a question asking, “What is the highest level of education you have completed?” and will be recorded at baseline. This will be a covariate.

Mental health diagnosis will be assessed by a single item at baseline (“Have you ever been diagnosed with a mental illness by a clinician?” Yes/No/Prefer not to say). This will be a covariate.

The cost of meditation practice will be assessed through self-reported questions asking participants whether they have spent any money related to their meditation practice, including on classes, courses, retreats, smartphone apps, resources such as mats, books, and clothes, and donations to meditation teachers or centers. These questions will be asked at baseline, monthly, and one year later.

The cost of mental health care use will be assessed via questions on type, frequency, and costs of psychological support. Specifically, participants will be asked, “In the past month, how many times did you see a… psychologist, psychiatrist, social worker, counselor, or other.” Participants will then be asked how they paid for this mental health service use (eg, “Out-of-pocket” and “Publicly funded”) and their out-of-pocket expenditure on mental health services in the past month. These questions will be asked at baseline, monthly, and one year. This will be used in the economic evaluation.

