### Sampling Plan

#### Hypothesis 1

Sample size calculation for quality of life measured by the EQ-HWB-9 using repeated measures linear mixed modeling assumes three groups will be assessed with (1) low, (2) medium, and (3) high regular meditation dosage. Given the limited research on the effects of long-term regular meditation practice, calculating power is challenging. We have therefore used conservative power calculations that may err on the side of underestimating the power of our primary analysis but allow for use of the effect information and analytic tools that are available. We have conducted power analysis using 3 levels of variation in the predictor of monthly meditation amount, rather than the continuous variable we plan to use in our final analysis. This is to allow for the use of an analytic power calculation method for our repeated measures design, rather than simulation measures, which would be highly speculative with the limited real and independent data available for our outcome measure [64]. Ten measurement time points were also used, rather than the 12 that will be included in our analysis, as this is the maximum for GLIMMPSE (University of Florida and University of Colorado Denver) power analysis software [65].

Sample size calculation for quality of life measured by the EQ-HWB-9 using repeated measures linear mixed modeling assumes three groups will be assessed with (1) low, (2) medium, and (3) high regular meditation dosage. No increase in EQ-HWB-9 scores was predicted for the low meditation group [58]. For the high meditation group, we estimate a stepwise increase to a minimum of a 2.25-point EQ-HWB-9 increase (out of a possible 9‐45 points) from baseline to time point 5, corresponding to the change in EQ-HWB-9 from baseline to 6 months associated with improvement in mental health in a validation of the EQ-HWB-9 sensitivity to change [59]. We then predict a further 2.25-point increase to time point 10, for a total increase of 4.5 points. For the moderate meditation group, stepwise improvement was predicted with a minimum of a 2.25-point EQ-HWB-9 increase from baseline to time point 10. Baseline EQ-HWB-9 is set at 19.6, with an SD of 7.0, as per our nationally representative surveys [66]. Using GLIMMPSE [65] with 95% power and 0.05 2-tailed type 1 error rate, sample size was calculated at 435 participants. We estimated a 20% loss to follow-up over one year, bringing the sample size required to 522 participants.

#### Hypothesis 2

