### Analysis Plan

The statistical analyses used to test each of our hypotheses are described below and summarized in Table 2. We will conduct the exploratory cost-effectiveness analysis in Stata (StataCorp LLC; [69]) and all other statistical analysis in R (R Foundation for Statistical Computing; [70]). We will report descriptive statistics (mean and SD if normally distributed, median and range if not) of all the variables included in the analyses. For all the analyses involving linear regression, we will check if the assumptions of linear regression are met by inspecting the residual plots for linearity, homogeneity of variance, normality, independence of residuals, and collinearity. If basic assumptions are not met, we will attempt to meet them via variable transformation, and failing that, we will use robust regression methods.

To ensure we only analyze responses from genuine participants, we will exclude participants from the study who give impossible or mutually incompatible responses as soon as they are detected [71]. As the primary strategy to handle missing data, the longitudinal constrained analysis assumes that the probability of missing outcome data is not related to the missing data but to some of the observed data in the model (missing at random [MAR]). Our models will use a restricted maximum likelihood (REML) estimator to handle missing data. The use of the REML estimator will enable us to effectively handle the potential bias introduced by differential attrition, as it allows for the estimation of unbiased fixed-effects coefficients and appropriately accounts for the variability introduced by random effects.

In addition, we will perform sensitivity analysis to assess how robust our analysis of the primary outcome is to deviations from MAR. We will calculate censoring weights by investigating the baseline and time-varying predictors of attrition, including engagement and response to follow-up factors. We will then recalculate the primary analysis with inverse probability of censoring weighting [72].

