For hypothesis 1, we will perform linear mixed model analysis of the fixed effect of the amount of meditation in the past month on quality of life in the past week (EQ-HWB-9), controlling for the potentially confounding baseline factors of age, caring status, education, mental health diagnosis, commitment to meditation practice, and membership of a meditation practice community at baseline. This model will allow us to assess how meditation as practiced by our participants under naturalistic conditions contributes to their quality of life, controlling for baseline differences related to time available for practice, symptom severity, motivation, and social support. If we detect an effect of meditation practice, we will perform sensitivity analysis to examine how robust this effect is to time-varying confounders by using inverse probability weighting of meditation in the last month to examine if the association would still be present if practice that month had varied independently of prior practice and benefit.

For hypothesis 2, we will perform linear mixed model analysis of the fixed effect of the amount of meditation in the past month on mental well-being in the past 2 weeks (SWEMWBS), controlling for the potentially confounding factors of age, caring status, education, mental health diagnosis, commitment to meditation practice, and active membership of a meditation practice community at baseline. If we detect an effect of meditation practice, we will again perform time-varying confounding sensitivity analysis with inverse probability weighting.

For hypothesis 3, we will add the variable capturing whether participants practiced secular meditation traditions (with no more than one month of reported practice in a spiritual tradition) versus engaging in spiritual traditions and its interaction term with the amount of meditation to the model for hypothesis 1. This initial analysis will allow us to assess whether predominantly secular meditation has a differential effect from meditation that incorporates spiritual practices, as practiced in real-life contexts, while retaining sufficient power. If we detect an effect, we will perform further exploratory analysis into what may be driving this difference. We will also describe the groups in terms of meditation practice characteristics, including proportion of practice types and social context.

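### Table 1 reads a significant slope on past-month meditation amount as a linear effect; a single slope cannot show that, and the reading does not fit the Analysis Plan's own transformation fallback

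*Protocol article*

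**What the plan says.** The interpretation column of Table 1 (section This Study) fixes in advance what a significant result means. For Hypothesis 1, a significant association "will suggest that regular meditation practice after initial instruction increases/decreases quality of life in a linear fashion". For Hypothesis 2, it is taken to mean that practice "increases/decreases mental well-being in a linear fashion".

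The model behind the H1 reading is given under Analysis Plan: "we will perform linear mixed model analysis of the fixed effect of the amount of meditation in the past month on quality of life", adjusted for baseline covariates. The Sampling Plan describes its three dose levels as a device for the power calculation, used "rather than the continuous variable we plan to use in our final analysis". Amount is built from weekly reports of "how many days they practiced in the past week, the average number of sessions per day, and the average minutes per session" (Measures). No spline, quadratic or dose-category term is named for the analysis, and no cap or transformation of amount is set in advance.

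The Analysis Plan does provide for checking assumptions in every analysis that involves linear regression, by "inspecting the residual plots for linearity, homogeneity of variance, normality, independence of residuals, and collinearity". If assumptions fail, variables are to be transformed and, failing that, robust regression is to be used.

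**The concern.** The test and the sentence attached to it answer different questions. The test asks whether the average slope differs from zero. The sentence says what shape the relation has. Any broadly rising relation gives a non-zero slope, including one that rises early and then levels off, or one that is flat until some amount and then steps up. The shape matters to readers: a straight line says that each further hour brings the same gain, while a plateau says that it does not.

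There is a second, conditional worry. Total practice time is often right-skewed, and the article foresees intensive periods, since its cost questions cover spending "including on classes, courses, retreats, smartphone apps". If a few months hold far more practice than the rest, they have high leverage on a straight-line scale. Such points pull the fit towards themselves, so residual plots can miss them. Some robust methods, such as M-estimation, down-weight large residuals rather than extreme exposures, and the article does not say which method is meant.

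**Working it through.** The article gives no figure on this point to reproduce; the sample sizes do not bear on it.

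**1. The passages side by side.** Table 1 concludes linearity from significance, with no condition. The Analysis Plan allows amount to be transformed if linearity looks doubtful. Suppose it becomes log(1+hours). One extra hour then changes the score by the coefficient times ln(8/7) = 0.134 at 6 hours a month, and by the coefficient times ln(22/21) = 0.047 at 20 hours, a ratio of about 2.9. A significant coefficient on that scale is an effect with diminishing returns, yet Table 1 would still call it linear. The two passages cannot both be followed as written.

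**2. Does a significant slope imply a line?** This was checked by simulation.
- From the article: 435 participants (the H1 number before dropout), 12 monthly measurements, SD 7.0, and an effect size of 2.25 points.
- Assumed: within-person correlation 0.6; usual practice lognormal with median 6 h/month (log-SD 0.5 between and 0.4 within persons); 0, 0.5% or 1% of months with 40 to 100 extra hours.
- Fit: random-intercept model by generalised least squares with known variance components, two-sided 5% test, 400 runs per setting.
- True response to H hours in the month: linear 0.15 × H; plateau 2.25 × min(H, 10)/10; threshold 2.25 if H > 10, otherwise 0.

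Each cell gives the results for 0 / 0.5% / 1% high-practice months:

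| True response | Linear slope significant | Mean slope (points/h) | Quadratic term significant |
|---|---|---|---|
| Linear | 100 / 100 / 100% | 0.148 / 0.150 / 0.150 | 4.8 / 5.8 / 4.2% |
| Plateau | 99.5 / 94.5 / 89.8% | 0.083 / 0.036 / 0.026 | 94.0 / 97.8 / 99.0% |
| Threshold | 100 / 100 / 100% | 0.132 / 0.059 / 0.047 | 88.0 / 100 / 100% |

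The slope is significant in about 90% to 100% of runs whatever the shape, so its significance carries almost no information about linearity. One added quadratic term does separate the shapes: it is significant in 88% to 100% of the non-linear runs and in about 5% of the linear ones.

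**3. Could a few months decide the slope?** Let a fraction p of months have amount X, and let the rest have mean m and SD s. The high months carry this share of the exposure variance:

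p(X − m)² / [p(X − m)² + s²]

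With p = 0.01, m = 400, s = 250 and X = 3000 minutes: 0.01 × 2600² = 67,600, and 67,600/(67,600 + 62,500) = 52%. With m = 600, s = 400 and the same X: 57,600/(57,600 + 160,000) = 26%. Over m = 400 to 600 and s = 250 to 400, the share is 26–52% at 3000 minutes, 45–70% at 4200 and 65–83% at 6000. For a lognormal amount with median 400 minutes and log-SD 0.6 to 1.2, the top 1% of months carries 26% to 61%.

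In the simulation of step 2, if usual practice does nothing and only the high months score 2.5 points more, the raw slope is significant in 4.5 / 60.2 / 92.8% of runs at 0 / 0.5 / 1% of months. Capping amount at 20 h lowers this to 11.2 / 33.2% at 0.5 / 1%, and log amount to 19.8 / 52.8%. Either change weakens the pull of such months without removing it.

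**The case against.** The strongest reply is that the article does look at linearity, names it first among its checks, and already has transformation as a remedy. It also plans medians and ranges for non-normal variables, so extreme months would be seen, and it excludes participants with impossible or incompatible answers. Caps, splines and influence checks are commonly left to an analysis plan. Table 1 says only that a result suggests an effect, and its closing words could be read as naming the fitted form.

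Most of this stands. It rules out saying that linearity goes unexamined; the accurate statement is that no formal test or non-linear term is specified. It does not rescue Table 1, because the published interpretation is unconditional and a later analysis plan would have to contradict it.

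Three stronger readings are tempting and are not supported:
- *Retreat months will dominate the slope.* The only textual basis is one word in a list of costs. No frequency or length is given. The cohort is beginners, and monastics and residents of religiously affiliated dwellings are excluded. At 1% of months, independent across the year, 1 − 0.99¹² = 11% of participants would have at least one such month, which is an assumption and not a finding.
- *The team's own data already show non-linearity.* Its survey "found a dose-response plateau between historical practice hours and psychological well-being outcomes after 500 hours of practice", but those are lifetime hours, observed cross-sectionally. Reaching 500 hours within the year needs 500/12 ≈ 42 h a month; at 6 h a month a participant accrues 72 h. The plateau is a reason for caution about shape and no more.
- *The tests lose their power.* One assumed scenario (600 people, benefit following log usual practice, retreat hours of 40 to 100 adding nothing) takes power from 97% to 49% or 29% with 1% or 2% retreat months. The plateau scenario above leaves it near 90%. The answer depends on the inputs chosen.

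**Conclusion.** The point holds for the interpretation rule. Significance of a single slope does not support the linear reading in the H1 and H2 rows of Table 1, and that reading conflicts with the transformation fallback. The 90–100% figure rests on the assumed exposure and effect shapes, but the principle does not depend on them.

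Influence of very-high-practice months is possible and of unknown size. It becomes serious only if amount is strongly right-skewed, and the article gives no distribution from which to judge. A reader might infer that log or capped amount should replace raw amount as the primary exposure, or that intensive months should be removed. The article does not support either. It aims to study meditation as people actually practise it, and both changes alter the quantity estimated. The H1 and H2 tests remain valid as tests of an average linear trend. What needs changing is what may be concluded from them.

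**What to change.** 1. Keep the one-coefficient tests for H1 and H2. In both rows of Table 1, replace the linear claim with a positive or negative linear trend (average association), on whatever scale amount is finally entered.
2. Pre-specify one non-linear term, such as a restricted cubic spline with stated knots or a quadratic, and describe the dose-response shape from that fit with its confidence band. Do not treat a non-significant departure as proof of linearity.
3. Add a sensitivity analysis with log(1+amount), or with amount capped at a pre-stated percentile, beside the raw slope. Report whether the conclusion depends on a few very-high-practice months. Since neither version removes their pull entirely, agreement between the fits is reassuring but not conclusive.

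The cost is wording, a few extra model fits and a slightly more cautious conclusion. No new data are needed. The article reports recruitment still under way in May 2026, so this can be settled before outcomes are analysed.
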